### Extracorporeal cardiopulmonary resuscitation for refractory OHCA

Refractory cardiac arrest, defined as the failure to achieve sustained return of spontaneous circulation (ROSC) despite prolonged CPR efforts or multiple defibrillation attempts, is associated with an even worse prognosis [5]. It is estimated that greater than 70% of patients with shockable OHCA are refractory to conventional CPR and remain pulseless on arrival at the emergency department (ED) [6]. Extracorporeal cardiopulmonary resuscitation (ECPR) is the application of extracorporeal membrane oxygenation (ECMO) or extracorporeal life support (ECLS) in patients with refractory cardiac arrest, aiming to immediately reconstitute the cardiopulmonary function outside patients’ bodies and thus buy time for the delivery of interventions necessary to regain an adequate native circulation [7]. As the most efficient approach of resuscitation for refractory cardiac arrest, the number of ECPR runs has increased tenfold over the last decades [8]. Multiple observational studies have supported the use of ECPR in refractory OHCA [9]. Encouragingly, in expert institutions with highly dedicated and well-trained ECPR teams, a > 40% functionally intact survival of refractory OHCA could be achieved [9, 10]. However, recent randomized controlled trials (RCT) have reported seemingly inconsistent results of ECPR for refractory OHCA [11–13]. Latest update on Adult Advanced Cardiovascular Life Support (ACLS) from the ILCOR Consensus on Science With Treatment Recommendations recommendation assigns a IIa recommendation for use of ECPR in patients with cardiac arrest refractory to standard ACLS [14].

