While first responders’ actions are critical to grab the chance of survival in patients with OHCA, studies have shown that the probability of survival with good functional recovery declines rapidly with each minute of CPR surpassing the effective duration, and that repeating the same therapies that did not work during this window did not yield significant survival benefits [15]. To boost the survival without severe impairment in patients with refractory OHCA, efficient strategies to minimize the low-flow duration should be considered. According to the Extracorporeal Life Support Organization guideline, ECPR should be considered after 10–15 min of unsuccessful conventional resuscitation efforts [7]. Observational data suggested that time to ECMO inversely correlated with neurologic outcomes in patients receiving ECPR [16]. In view of the inherent drawbacks of time elapsed in prehospital resuscitation in OHCA, as reflected in three published RCTs (the average interval from emergency calls to ECMO initiation was 59 min, 62 min, and 74 min, respectively), we believe that the benefits of ECPR for refractory OHCA should be investigated in the context of more timely application [17]. The similar result from retrospective data in ECPR also demonstrated 60 min between arrest-to-ECMO was an important factor for better neurological outcome [18].

To add to the evidence on the effectiveness of ECPR for patients with refractory OHCA with longer duration of low-flow time, we propose the present prospective randomized open label clinical trial. The centers are all experienced centers in performing ECPR and coronary intervention and located in the Taipei metropolitan area.

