### EMS in Taipei metropolitan area

In response to emergency calls for OHCA events, the Taipei Metro EMS system proceeds with instant online dispatcher-assisted CPR by witnessed bystanders with or without a public automatic external defibrillator (AED) at the same time as EMS team dispatching. On arrival at the scene, the EMS team will perform ACLS, including high-quality chest compression, basic or advanced airway management, intravenous or intraosseous access establishment, or automated chest compression by the Lund University Cardiopulmonary Assist System, and AED defibrillations if needed, followed by intra-arrest escorted transportation with continuous telecommunication to emergency service of the Taipei Metro major disease emergency responsible hospitals in the Taipei Metro OHCA Total Care Consortium.

The Taipei metropolitan area has a densely distributed healthcare system. Based on recent data, the mean EMS response time (from emergency call to arrival at scene) is 6.4 ± 3.3 min, and the mean EMS transport time (from scene to ED arrival) is 4.5 ± 2.8 minutes [19]. Since the some buildings without elevator and the EMS had standard procedures to be performed on scene, and the area of New Taipei City is 7 times than Taipei City, we estimate the mean time from call to ED arrival approximately 40–60 min.

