#### Intervention—ECMO initiation

After randomization, if the enrolled patient has stable ROSC before initiating ECMO, he/she will be transferred to the cardiac catheterization laboratory (CCL) without ECMO support. The indications for ECMO include no ROSC or unstable ROSC (persistent or recurrent VF or pVT, profound cardiogenic shock with systolic blood pressure (BP) < 90 mmHg or mean BP < 60 mmHg despite intense inotropic support (bolus of epinephrine > 3 bolus), or persistent hypoxia with arterial oxygen saturation (SaO2) < 90% despite maximal ventilation support). The femoral artery and vein access will be cannulated under ultrasound guidance. ECMO would be deemed futile if more than one discontinuation criterion suggesting ineffective resuscitation (end-tidal carbon dioxide < 10 mmHg, partial pressure of oxygen in arterial blood < 50 mmHg or oxygen saturation < 85%, or serum lactate > 20 mmol/L) has been met.

However, if unstable ROSC persists as defined above, ECMO is initiated according to the randomization arm protocol. For the emergency total ECLS group (Fig. 1), the veno-arterial ECMO (VA-ECMO) will be initiated within 15 min after randomization. For standard ACLS with the recue ECMO group, patients will receive 15 min of ACLS at ED first. If there is no stable ROSC, the futility of ECLS would be reevaluated. Therefore, the recue VA-ECMO should be initiated after 15 min since randomization.

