### Statistical analysis

#### Sample size rationale

The trial is designed to demonstrate a treatment effect on the primary endpoint. Accepting a power of 80% and a level of significance of 5%, the sample size is calculated using a two-sided chi-square test. In reference to published multicenter trials, we estimate a 30-day neurologically favorable survival of 25% and 12% in the emergency total ECLS group and the standard ACLS with rescue ECMO group, respectively. Assuming a 10% dropout rate, we plan to enroll 186 participants per arm (roughly 200). No interim analysis is planned. If interim analysis is deemed necessary determined by Consortium committee, we will conduct one interim analysis 1 year after enrollment, and the statistical testing will be adjusted to this accordingly. The flowchart of intention to treatment and per protocol are attached in supplement.

All patients enrolled in the study will be analyzed primarily on an intention-to-treat basis. Continuous variables will be reported as mean ± standard deviation or median with interquartile range. Categorical variables will be presented as frequency. A logistic regression model with the stratification variable (center) will be conducted to evaluate the primary efficacy endpoint by treatment group. Odds ratios are to be calculated as effect estimates with 95% confidence intervals. Patients whose primary outcome cannot be assessed will be regarded as failures.

Per-protocol analysis, which only includes patients who adhere to the allocated protocol, will be performed to minimize the impact of non-adherence or deviations from the strict protocol.

For patients randomized to the total ECLS group, if ECPR is not required due to stable ROSC at ED or ECMO is initiated after 20 min since arriving at ED or after 60 min since emergency calls, they would be excluded from per-protocol analysis. Similarly, for patients randomized to the standard ACLS with rescue ECMO group, if ECMO is initiated within 20 min of arriving at the ED or within 60 min of emergency calls, they would be considered crossover and excluded from per-protocol analysis.

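### The per-protocol set drops protocol-adherent stable-ROSC patients from the ECLS arm only; alone this lowers the ECLS rate, though the net direction of the per-protocol comparison is undetermined

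*Protocol article*

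**What the plan says.** All references are to the protocol article. The per-protocol rules stand under Statistical analysis, Sample size rationale.

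- **Definition of the set:** "Per-protocol analysis, which only includes patients who adhere to the allocated protocol".
- **ECLS arm:** a patient is dropped "if ECPR is not required due to stable ROSC at ED or ECMO is initiated after 20 min since arriving at ED". A start of ECMO more than 60 min from the emergency call is a further ground for exclusion.
- **Control arm (standard ACLS with rescue ECMO):** a patient is dropped "if ECMO is initiated within 20 min of arriving at the ED or within 60 min of emergency calls, they would be considered crossover". Stable ROSC is not listed.
- **What the protocol tells sites to do** (Intervention—ECMO initiation): "if the enrolled patient has stable ROSC before initiating ECMO, he/she will be transferred to the cardiac catheterization laboratory (CCL) without ECMO support". This applies to enrolled patients after randomisation and does not distinguish the arms.

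The primary analysis is by intention to treat. Flowcharts for the two analysis sets are said to be in a supplement, which is not at hand.

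**The concern.** The ECLS-arm clause contradicts the definition a few lines above it. A patient who regains stable circulation before cannulation and goes to angiography without ECMO has been treated as the protocol directs, yet is removed as if non-adherent.

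The clause also acts on one arm only. Stable ROSC is a post-randomisation event that can occur in either arm, but it leads to exclusion only under ECLS. If these patients do better than average, the ECLS rate falls through selection alone while the control rate is untouched by this rule.

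At stake is how the supporting analysis is read. A reader who sees a per-protocol effect smaller than the intention-to-treat effect would normally look for an explanation in adherence. Here part of the gap could come from how the set was built.

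**Working it through.** **Inputs from the article.** Expected favourable 30-day survival is 25% (ECLS) and 12% (control). The article gives no share of patients with stable ROSC before ECMO and no outcome for them, so there is no figure of its own to reproduce. Indirect support for a better prognosis is the statement in the Introduction that failure to achieve sustained ROSC "is associated with an even worse prognosis".

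**Assumptions.** Let r be the share with stable ROSC before ECMO and f their favourable-outcome rate, both equal in the two arms. Let p be the whole-arm rate.

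**Step 1: the stable-ROSC rule alone.** ECLS per-protocol rate = (p − r·f)/(1 − r). It is below p whenever f > p. Control stays at its whole-arm rate.

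| Case | r | f | ECLS | Control | Difference |
|---|---|---|---|---|---|
| Planned rates | 10% | 50% | (0.25 − 0.05)/0.90 = 22.2% | 12% | +10.2 points (planned +13) |
| Planned rates | 20% | 50% | (0.25 − 0.10)/0.80 = 18.75% | 12% | about +6.7 |
| No effect, 18.5% per arm (midpoint of 25% and 12%) | 10% | 50% | (0.185 − 0.05)/0.90 = 15.0% | 18.5% | −3.5 |
| No effect, 18.5% per arm | 20% | 50% | (0.185 − 0.10)/0.80 = 10.6% | 18.5% | −7.9 |

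Odds ratios at r = 10%, f = 50%: 2.10 instead of 2.44 under the planned rates, and 0.78 instead of 1.00 under no effect. Keeping stable-ROSC patients in both arms returns both comparisons to their whole-arm values as far as this rule is concerned.

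**Step 2: which assumptions are possible.** With equal r and f in both arms, favourable outcomes among control stable-ROSC patients make up r·f of that arm, which cannot exceed 12%. Over r = 10–30% and f = 40–60% with r·f ≤ 0.12:

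- Largest difference, r = 10%, f = 40%: (0.25 − 0.04)/0.90 = 23.3%, or +11.3 points.
- Smallest difference, r = 20%, f = 60%: (0.25 − 0.12)/0.80 = 16.25%, or about +4.3 points.

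The corner r = 30%, f = 60% would give (0.25 − 0.18)/0.70 = 10.0%, or −2.0 points. It needs 18% of control patients to do well through stable ROSC alone, which is impossible beside a 12% control rate.

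**Step 3: the other exclusions in the paragraph.** Late-ECMO patients leave the ECLS arm, and the Introduction says "time to ECMO inversely correlated with neurologic outcomes in patients receiving ECPR", so this tends to raise the ECLS rate. Early-ECMO patients leave control, which may lower the control rate. With no true effect (18.5% per arm), f = 50%, an assumed 20% late ECMO with 5% success and 20% early ECMO in control with 30% success:

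- r = 5%, stable-ROSC rule alone: (0.185 − 0.025)/0.95 = 16.8%, a difference of −1.7 points.
- r = 5%, adding late ECMO: (0.185 − 0.025 − 0.01)/0.75 = 20.0%, or +1.5.
- r = 5%, adding early ECMO in control, (0.185 − 0.06)/0.80 = 15.6%: +4.4.
- r = 20%, all three rules: (0.185 − 0.10 − 0.01)/0.60 = 12.5% vs 15.6%, or −3.1.

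The sign therefore depends on shares that the article does not give. Considering only the two ECLS-arm rules, the late share that cancels the stable-ROSC effect is r(f − p)/(p − q), where q is the late-ECMO success rate. At r = 10%, f = 50% this is 0.0315/0.135 = 23% for q = 5%, and 0.0315/0.085 = 37% for q = 10%.

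**Step 4: could late ECMO be that common?** Under EMS in Taipei metropolitan area the article says "we estimate the mean time from call to ED arrival approximately 40–60 min". Assume a normal arrival time with SD 8–15 min, truncated at 60 min, and ECMO 15 min after arrival. Then about 26% to 94% of ECLS-arm patients who need ECMO would start after 60 min. Table 3, by contrast, estimates 45 min or less from call to ECLS, which would make late starts uncommon. The documents do not settle it.

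**The case against.** The strongest reply is that this clause cannot be judged alone. A reader might infer that the per-protocol comparison as a whole is biased against ECLS. The timing exclusions in the same paragraph can offset or outweigh the clause, so the documents do not support that. It follows that deleting the clause need not reduce the total bias. With no true effect, r = 10%, f = 50% and 20% late ECMO at 5% success, the present rule gives (0.185 − 0.05 − 0.01)/0.70 = 17.9%, a bias of −0.6 points. Without the clause it is (0.185 − 0.01)/0.80 = 21.9%, a bias of +3.4. Both arguments stand. They do not justify removing adherent patients from one arm, because a bias of unknown size is not a correction for another.

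Two further points stand. The article never says that stable-ROSC patients have the best prognosis; it supports a better one only indirectly. The consequence is also limited: intention to treat is primary, and the per-protocol analysis is offered to limit the impact of non-adherence, not as confirmatory.

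The supplement's flowchart might treat control differently. But the article states explicit rules for each arm, and nothing in it points to a matching control rule.

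**Conclusion.** The point holds in this form: the stable-ROSC exclusion contradicts the set's own definition and conditions on a post-randomisation event in the ECLS arm only. Taken alone, it lowers the ECLS per-protocol rate whenever these patients do better than their arm's average. On assumed figures compatible with a 12% control rate, the planned 13-point difference becomes about 11.3 to 4.3 points. With no true effect, 10% stable ROSC and 50% favourable outcome it produces 15.0% vs 18.5%. All shares and outcomes for these patients are assumptions, taken as equal in the two arms.

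Two stronger readings are not supported. The net direction of the per-protocol comparison is undetermined. Nor does this clause turn the planned benefit into apparent harm: within the compatible range examined the difference shrinks but stays positive. The primary intention-to-treat result is not affected.

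**What to change.** Remove the stable-ROSC exclusion from the per-protocol paragraph. State that a patient in either arm who has stable ROSC before ECMO and is managed as the section on ECMO initiation directs is adherent and stays in the per-protocol set. Align the supplementary flowchart if it repeats the present rule.

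Report the per-protocol result as supportive only, and note that the remaining timing exclusions also condition on post-randomisation events differently by arm. The change makes the stable-ROSC rule symmetric and consistent with the definition; it should not be described as making the set unbiased.

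The cost is one clause and one sentence of caution, fixed before outcome data by arm are seen. Treatment, sample size and data collection do not change.

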**Interventions:**

Participants are assigned to: (1) emergency total ECLS, with initiation as soon as possible after randomization and within 60 min of the emergency call, or (2) standard ACLS with rescue ECLS, in which at least 15 min of standard ACLS is provided in the ED before ECLS is considered. Both groups receive immediate coronary angiography and percutaneous coronary intervention (PCI) when indicated, and active LV unloading is recommended according to prespecified criteria.

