### Enrollment and randomization of trial population

Refractory OHCA is defined as cardiac arrest in patients transported to hospital with ongoing CPR. Upon receiving the EMS’s referral of OHCA patients, the OHCA response team, composed of emergency physicians, interventional cardiologists, and cardiac surgeons, will evaluate the eligibility of patients based on on-scene information. The inclusion and exclusion criteria are described in Table 1. When the patient arrives at the ED, a rapid screening is performed to reassure his/her eligibility. All eligible patients will be randomized into the emergency total extracorporeal life support (total ECLS) group and the standard advanced cardiac life support with rescue ECMO (**standard ACLS**) group (Fig. 1).

**Table 1 Tab1:** PreInclusion and exclusion criteria

Screening inclusion criteria	Pre randomization Exclusion	Post-randomization exclusions criteria
• Aged 18–75 years old	• Age under 18 or over 75	• Age < 18 years or > 75 years old
• Witnessed cardiac arrest with bystander cardiopulmonary resuscitation	• Major trauma	• Initial non-shockable rhythm, i.e. pulseless electrical activity or asystole
• Initial shockable rhythm, i.e. ventricular fibrillation or pulseless ventricular tachycardia	• Initial non-shockable rhythm	• Acute aortic dissection
• Need for repeated defibrillation shocks (> 2) by external defibrillator	• Major trauma	• Acute massive pulmonary embolism
• Estimated transportation time from activation of the emergency response system to arrival at emergency department of participant institutions less than 60 min	• Suicide, illicit drug overdose or intoxication	• Acute intracerebral hemorrhage
	• Pre-arrest mRS > 3 or CPC > 2	• Major trauma due to blunt, penetrating or burn injury
	• Unwitnessed CPR	• Severe peripheral artery disease
		• Known pregnancy
		• Suicide, illicit drug overdose or intoxication
		• Known pre-arrest mRS > 3 or CPC > 2
		• Active malignancy with a life expectancy of less than 1 year
		• Effective DNR order
		• Absolute contraindications to emergency coronary angiography, including known anaphylactic reaction to angiographic contrast media, acute bleeding

CPC, cerebral performance category; DNR, do-not-resuscitation; mRS, modified Rankin score

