**Fig. 1 Fig1:**
[figure not shown]
Study flowchart. Before arriving at ED, the eligibility of OHCA patients will be evaluated by the OHCA response team of the receiving hospital, based on on-scene information provided by EMS. For eligible OHCA patients, randomization will be completed within 5 min of arrival at ED. After CT imaging, patients of first enrollment will be checked again if any exclusion criteria are met. Only patients who received early coronary angiography and/or intervention will be included in the final analysis. ACLS: advanced cardiovascular life support; CCL: cardiac catheterization laboratory; CPC: cerebral performance category; CPR: cardiopulmonary resuscitation; CT: computed tomography; ECLS: extracorporeal life support; ED: emergency department; EKG: electrocardiography; EMS: emergency medical services; mRS: modified Rankin scale; OHCA: out-of-hospital cardiac arrest; ROSC: return of spontaneous circulation; ECG: echocardiography

Randomization is performed immediately upon ED arrival (target: within 5 min) for patients meeting inclusion criteria and experiencing refractory cardiac arrest (defined as ongoing CPR on arrival). Patients with stable ROSC before randomization (defined as sustained pulse with systolic BP ≥ 90 mmHg without ongoing chest compressions for ≥ 2 min) are not randomized and proceed directly to coronary angiography.

Patients with unstable ROSC defined as: (1) return of pulse but requiring ongoing chest compressions, (2) recurrent VF/VT requiring repeated defibrillation, (3) persistent profound hypotension with systolic BP < 90 mmHg or mean BP < 60 mmHg despite vasopressor support, or (4) intermittent epinephrine injection to maintain the heart beating are eligible for randomization."

A computerized randomization list is provided by the National Taiwan University Hospital Clinical Trial Center by a software app (REDCAP). The randomization is in 1:1 ratio, stratified by participant hospitals, with a permuted block of 4. In-hospital randomization is conducted by OHCA response team coordinators immediately after the eligible patients arrive at ED. The randomization codes will be maintained by the National Taiwan University Hospital Clinical Trial Center and monitored by the Data Safety Monitoring Committee. The EMS teams and intensivists in the cardiac intensive care unit (ICU) will be blinded to the study group assignment and follow the institutional standards for post-cardiac arrest care.

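### The standard ACLS arm's per-protocol crossover rule excludes patients treated as assigned, and the two arms' 60-min call clauses select on arrival time in opposite directions

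*Protocol article*

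**What the plan says.** **Entry and randomisation.** Table 1 of the protocol article admits patients by time to the ED: "Estimated transportation time from activation of the emergency response system to arrival at emergency department of participant institutions less than 60 min". The Fig. 1 legend states that "randomization will be completed within 5 min of arrival at ED".

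**Treatment timing.** Under Intervention—ECMO initiation, ECMO in the total ECLS group "will be initiated within 15 min after randomization". For the control group, after 15 min of ACLS in the ED, "the recue VA-ECMO should be initiated after 15 min since randomization". The abstract (Interventions) also requires at least 15 min of ED ACLS in the control arm. For total ECLS it adds a limit counted from the call: "with initiation as soon as possible after randomization and within 60 min of the emergency call". Table 3 likewise allows up to 60 min from call to ECLS. No section other than the per-protocol rules sets an earliest time from the call for rescue ECMO.

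**Per-protocol rules** (Statistical analysis, under Sample size rationale). A total ECLS patient is excluded if ECMO was not needed because of stable ROSC, or if "ECMO is initiated after 20 min since arriving at ED or after 60 min since emergency calls". A control patient is a crossover, and excluded, "if ECMO is initiated within 20 min of arriving at the ED or within 60 min of emergency calls".

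**Primary analysis.** "All patients enrolled in the study will be analyzed primarily on an intention-to-treat basis".

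**The concern.** A per-protocol set should keep patients who received the assigned strategy. For the control arm that strategy is 15 min of ED ACLS followed by rescue ECMO if needed. A rule counted from the emergency call measures something else as well, namely how long the patient took to reach hospital. An early-arriving control patient can have the full ACLS period and still be labelled a crossover.

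In the total ECLS arm the same 60-min mark works the other way. The trial admits patients who reach the ED up to 60 min after the call and then limits ECMO to 60 min after the call, so a late arrival has little or no time left, however prompt the team.

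Together the clauses tend to keep early arrivals in one arm and late-arriving ECMO recipients in the other. The subgroup section itself treats low-flow time as critical to neurological outcome. At stake is whether the per-protocol comparison is between like patients.

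**Working it through.** **Inputs.** A = minutes from call to ED arrival, below 60 (Table 1). r = arrival to randomisation, 0–5 min (Fig. 1 legend). c = randomisation to flow in total ECLS, at most 15 min. d = randomisation to flow in control, at least 15 min (both from Intervention—ECMO initiation). Per-protocol cut-offs are 20 min from arrival and 60 min from the call. The expected mean of A is 40–60 min (EMS in Taipei metropolitan area). Cannulation time after a decision is not given; 12 min is assumed, the mean randomisation-to-ECLS time that Table 3 lists for one earlier trial.

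**1. Where the cut-offs come from.** The 20-min limit is the sum of the two treatment limits: 5 + 15 = 20. The 60-min limit has a source for total ECLS (abstract, Table 3) but none for control.

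**2. Control, call clause.** Flow is at A + r + d. The patient is a crossover if A + r + d ≤ 60, that is A ≤ 60 − r − d.
- No cannulation time (d = 15): A ≤ 45 with r = 0; A ≤ 40 with r = 5.
- With 12 min (d = 15 + 12 = 27): A ≤ 33 with r = 0; A ≤ 28 with r = 5.

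Example on paper: arrive 30, randomise 35, ACLS to 50, ECMO at 55. That is 25 min after arrival and 20 min after randomisation, as directed, but 55 < 60, so crossover. Example with 12 min for cannulation: arrive 25, randomise 28, ACLS to 43, ECMO at 55; again crossover.

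To stay in, a patient arriving at 30 needs ECMO more than 30 min after arrival. The earliest correct time is 15–20 min after arrival with no cannulation time (a gap of 10–15 min), or 27–32 min with 12 min (a gap of at most 3 min).

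**3. Control, 20-min clause.** Randomise at 1 min, ACLS to 16, ECMO at 18 min after arrival: correct, but 18 < 20, so crossover. With 12 min for cannulation, flow is at 27 min or later and the clause does not bite.

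**4. Total ECLS, call clause.** Excluded if A + r + c > 60.
- r = 5, c = 15: A > 40. r = 0, c = 15: A > 45.
- c = 12: A > 60 − 12 − 5 = 43, up to A > 60 − 12 − 0 = 48.
- Time left from arrival to flow, 60 − A: 15 min at A = 45, 10 at 50, 5 at 55.

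Example: arrive 50, randomise 52, ECMO at 65. This meets the 5-, 15- and 20-min limits (2, 13 and 15 min) but breaks the 60-min limit.

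**5. Illustration only.** No spread of call-to-ED time is given. Assume a normal distribution truncated to 10–60 min, mean 40–50 and SD 6–10 before truncation.

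| Arrival to flow | Arm | Share of ECMO recipients excluded by the call clause |
|---|---|---|
| 15 min | total ECLS | about 20–79% |
| 25 min | control | about 1–32% |
| 30 min | control | about 0–16% |

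Mean arrival among those kept is 35–42 min in total ECLS (15 min to flow) and 42–50 min among control ECMO recipients (25 min to flow). At assumed means of 45 or 50, most of that gap arises in the total ECLS arm.

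**6. Table 3 (minor).** A mean call-to-ECLS of 45 min or less requires flow within 45 − 40 = 5 min of arrival at the lowest expected mean arrival, and is impossible above a mean of 45. From 40 min, 12–15 min gives 40 + 12 = 52 to 40 + 15 = 55. The Novelty section and the Discussion also expect longer times.

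**The case against.** **The 60-min limit defines the total ECLS strategy.** The abstract and Table 3 state it, so excluding a patient with flow at 65 min enforces the plan. This stands. A reader might infer that the per-protocol section adds a new limit to both arms and removes total ECLS patients who complied with the whole plan; the documents do not support that. What remains in this arm is a conflict between that limit and entry by time to the ED.

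**The control examples leave little or no time for reassessment and cannulation.** This largely stands. With 12 min allowed, the affected arrivals fall from 45 min or earlier to about 28–33 min or earlier, below the expected mean of 40–60 min, and the 20-min clause hardly matters. The rule is still wrong for those it catches, and the plan has a subgroup for arrivals under 30 min.

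**Direction of bias.** A reader might infer that the clauses favour total ECLS. The documents do not establish this. The same rules drop stable-ROSC patients, likely to do well, from the total ECLS arm only, which may pull the other way. Control patients who never receive ECMO stay in at every arrival time. Removing early-arriving refractory controls could raise or lower the control success rate.

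**Scope.** Per-protocol is secondary, and the article refers to an analysis flowchart in a supplement not seen here. Both limit the weight of the point; neither changes the stated rule.

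**Conclusion.** The control-arm rule is wrong as written. It labels as crossover patients who had the full 15 min of ED ACLS, and nothing elsewhere in the article supports an earliest time counted from the call. It reaches compliant ECMO recipients arriving by 45 min at the latest on paper, and by about 28–33 min under the 12-min cannulation assumption.

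In the total ECLS arm the limit is consistent with the stated intervention but not with the entry window or the expected arrival times; patients who meet all other limits can be excluded from an arrival time just over 40 min.

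Among ECMO recipients the two clauses select on a prognostic factor in opposite directions. That follows from the rules alone. The share of patients affected and the net bias cannot be determined from the article, and the intention-to-treat result is untouched. The change should be made before analysis. The Table 3 estimate is inconsistent but drives no analysis.

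**What to change.** - **Control rule:** delete the alternative counted from the emergency call, and replace the 20-min-from-arrival test with one definition: crossover means ECMO started before 15 min of ACLS after randomisation.
- **Total ECLS rule:** define adherence as ECMO within 15 min of randomisation and within 20 min of ED arrival, so that arrival time does not decide membership in one arm only.
- **60-min rationale:** examine it through the planned call-to-ED subgroups (under 30, 30–45, 45–60 min), which apply equally to both arms. They address it indirectly, since they use time to the ED rather than time to flow.
- **Table 3 (minor):** restate call-to-ECLS as above 40 min, and about 52–55 min or more at the lowest expected mean arrival.

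The cost is the wording of two rules and one table cell. Entry criteria, sample size and the primary analysis do not change. The real downside is that the per-protocol set no longer requires flow within 60 min of the call, which the sponsor may regard as part of the strategy. The control change corrects an error; the total ECLS change is a judgement in favour of comparable arms.
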